### *17.2 Statistical analysis*

Analysis will assess microbiota differences between the two study arms and between twin pairs. Microbiome composition will be analysed with respect to (1) species diversity, (2) compositional differences, and (3) differences in abundance of taxa. Analysis will be carried out using statistical programs STATA and RStudio. All analysis will take a hierarchical approach; crude models assessing just the variable of interest (prebiotic supplementation), and models adjusted for key biological (age, gender, exercise etc..) and technical covariates (e.g. differences in library size) will be applied.

Differences in species diversity and richness will be compared between each study arm in regression analysis in crude and adjusted models. Distance matrixes characterise the inter-individual differences in microbiota composition; ordination analyses and permutational multivariate analysis of variance (PERMANOVA) will be used to understand differences in composition between each study arm.

ASVs will be collapsed to family, order, and phylum levels, with hierarchical models, adjusted for each potential mediator individually, then fully adjusted. All models will be adjusted for multiple testing.

All twins within each study arm will be used in paired tests to assess if microbiota dissimilarity increased with differences in muscle strength, taking relevant covariates into consideration. An intention to treat analysis will be carried out to address participants who do not complete the study.

Secondary analyses will include linear mixed effects regression models to investigate associations between microbiota composition, microbial metabolite markers, markers of appetite and other lifestyle and physiological parameters including muscle strength (as measured by chair-rise time) adjusting for covariates and multiple testing.

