### ***b. Main Analyses***

Paired tests will be carried out to assess for differences between each arm at baseline; two sample t-tests for continuous variables (normally distributed), Mann-Whitney test for non-normally distributed continuous variables, and Pearson's chi-squared tests for categorical variables.

All primary statistical analyses will be unadjusted. Subsequent analyses carried out will be adjusted for relevant covariates which are known or suspected *a priori* to be associated with the outcome, as described henceforth. Stata and RStudio will be used for all statistical analysis.

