### **ii. Secondary Outcomes**

Secondary analyses will include linear mixed effects regression models to investigate associations between the change in each of the below variables, adjusting for covariates where relevant.

- Grip strength
- Short physical performance battery (SPPB) score
- IPAQ - physical activity questionnaire – either overall score or MET minutes/week
- Appetite - SNAQ questionnaire
- Cognition (as measured by CANTAB battery)
- Gut microbiome measures – function and composition (from faecal samples) [See Section 7.2.2.1 for further detail].
- Serum metabolites

The change in grip strength, SPPB score, IPAQ score, FI, cognition, and SNAQ will be analysed using the same method as for the primary outcome, including usage of the baseline value for the actual factor as a covariate.

An exploratory analysis will be carried out to assess for any differences in serum metabolite profile between the two arms of the study. Linear mixed models will be used as described in Section 7.2.1 using the metabolite at study end as the dependent variable and including the baseline level as a covariate. Analyses will be adjusted for multiple testing to control the overall type 1 error rate.

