## **1. Gut Microbiome Function and Composition**

Stool samples will be collected from all participants at the beginning and end of the study, via post. The DNA extraction will be carried out in our own laboratory, and then the extracted DNA samples will be sent to an external microbiome sequencing and bioinformatic company, who will carry out high-resolution shotgun metagenomics microbiome analysis of all samples. This includes full profiling of microbiota present (composition), functional species group association analysis, as well as measures of alpha and beta diversity for each individual sample.

Once the above information is available, statistical analysis will assess microbiota differences between the two study arms and between twin pairs. Microbiome composition will be analysed with respect to (1) species diversity, (2) compositional differences, (3) functional differences and (4) differences in abundance of taxa. All analysis will take a hierarchical approach; crude models assessing just the variable of interest (prebiotic supplementation), and models adjusted for key biological (age, sex, exercise etc.) and technical covariates (e.g., differences in library size) will be applied.

Differences in species diversity and richness will be compared between each study arm in regression analysis in crude and adjusted models. Distance matrixes characterise the inter-individual differences in microbiota composition; ordination analyses and permutational multivariate analysis of variance (PERMANOVA) will be used to understand differences in composition between each study arm.

ASVs will be collapsed to family, order, and phylum levels, with hierarchical models, adjusted for each potential mediator individually, then fully adjusted. All models will be adjusted for multiple testing.

All twins within each study arm will be used in paired and unpaired tests to assess if microbiota dissimilarity increased with differences in muscle strength, taking relevant covariates (including diet [HEI], BMI and frailty index) into consideration.

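### The taxa models adjust for unnamed, untimed potential mediators, and no model is named as the basis for the between-arm conclusion

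*Combined protocol and SAP*

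**What the plan says.** The SAP's microbiome section (cross-referenced there as 7.2.2.1) sets out a hierarchy in two places.

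- It first describes a general approach for all microbiome analyses: "crude models assessing just the variable of interest (prebiotic supplementation"), followed by "models adjusted for key biological (age, sex, exercise etc.) and technical covariates", with library size as the technical example.
- For taxa collapsed to family, order and phylum, it then plans models "adjusted for each potential mediator individually, then fully adjusted". Protocol 17.2 has the same instruction: "with hierarchical models, adjusted for each potential mediator individually, then fully adjusted".
- On multiplicity it adds: "All models will be adjusted for multiple testing".

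Two general statements under SAP Main Analyses also bear on this: "All primary statistical analyses will be unadjusted", and later analyses are to be "adjusted for relevant covariates which are known or suspected" in advance to relate to the outcome.

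Gut microbiome measures are a secondary outcome. The null hypothesis in SAP section 6 is that the change does not differ between the two arms.

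**The concern.** A mediator, in the usual sense, is a variable that the treatment changes and that in turn changes the outcome. Conditioning on it has two consequences. It removes from the arm coefficient whatever part of the effect passes through the mediator, leaving at best a direct effect. It also breaks the protection of randomisation: if mediator and taxon share an unmeasured cause, conditioning on the mediator lets that cause into the arm comparison.

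Neither result answers the null hypothesis in SAP section 6, which concerns the total difference between arms. Specific Aim 2 also asks for effect sizes on causal links from the prebiotic to microbiome composition. If the crude and fully adjusted models disagree for a taxon, the plan has no stated rule for which one counts.

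**Working it through.** There is no planned figure to reproduce, because the documents give no effect size, power or mediated share for taxa. The check is therefore a reading of the text followed by an illustration.

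**Are these variables fixed before randomisation?**

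- The microbiome section uses two different terms, biological and technical covariates in one paragraph and potential mediators in a later one. It does not equate them.
- No mediator is named. Of the covariates that are named, age and sex cannot be changed by a supplement. Exercise carries no time point.
- Physical activity and appetite are also outcomes: "The change in grip strength, SPPB score, IPAQ score, FI, cognition, and SNAQ will be analysed using the same method" as the primary outcome. The protocol flowchart (10.2) repeats the food diary and questionnaire before the final call. Post-randomisation values of diet, activity and appetite will therefore exist.
- The rule under Main Analyses selects covariates by their association with the outcome. It does not limit them to baseline values.

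**Which model carries the conclusion?** The crude model, the one-at-a-time models and the full model are all planned, and none is designated. The statement that primary analyses are unadjusted does not say whether it covers secondary outcomes such as taxa.

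**What would mediator adjustment do?** In a linear model with no mediator–taxon confounding,

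adjusted coefficient = total effect × (1 − m),

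where m is the share of the effect passing through the mediator.

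The illustration simulated 36 twin pairs with one twin per arm (the 36 per arm is from Supplementary Table S6). It used within-pair regression, a two-sided 0.05 test and 4,000 repeats. The assumed inputs, none of them from the documents, are a total effect of 0.60 SD, an arm effect on the mediator of 0.8 SD and an intra-pair correlation of 0.5.

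| Share mediated, m | 0.60 × (1 − m) | Adjusted estimate (power) | Crude estimate (power) |
|---|---|---|---|
| 0 | 0.60 | 0.61 (84%) | 0.60 (93%) |
| 0.25 | 0.45 | 0.45 (60%) | 0.60 (92%) |
| 0.50 | 0.30 | 0.30 (32%) | 0.60 (87%) |
| 0.75 | 0.15 | 0.15 (12%) | 0.60 (78%) |
| 1 | 0.00 | 0.00 (5%) | 0.60 (67%) |

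Crude power falls down the table because the mediator adds more variance to the outcome as m rises. The crude estimate stays at 0.60.

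**Can the bias go the other way?** Take no arm effect on the taxon at all, and an unmeasured common cause loading 0.5 on both mediator and taxon. Within arm, the mediator has variance 1 and covariance 0.5 × 0.5 = 0.25 with the taxon, so its coefficient is 0.25. The adjusted arm coefficient is then 0 − 0.25 × 0.8 = −0.20. The simulation gave −0.20, with rejection in 14.5% of repeats against 4.8% for the crude model. If one of the two loadings had the opposite sign, the result would be +0.20.

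**And if the adjusting variable is a baseline one?** With a baseline covariate (assumed coefficient 0.4), both models gave 0.60. Power was 85.3% crude and 92.5% adjusted. Adjustment then does no harm and gains precision.

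**The case against.** The strongest reply is that the randomised effect is not lost. The crude arm-only model appears in the same section, and setting it beside the adjusted steps is how attenuation would be seen. No sentence calls the fully adjusted model the treatment effect or bases the arm conclusion on it; coming last in a list does not make it so. This stands. A reader might infer that the plan will report a mediator-adjusted coefficient as its finding on taxa and so hide a real effect. The documents do not support that.

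A second reply is that potential mediator may be loose wording for baseline covariates. SAP section 4 takes the frailty and healthy eating indices from the most recent cohort data, and the subgroup list in section 5 specifies exercise level at baseline. The sentence also looks carried over from the protocol, since it refers to ASVs while the SAP plans shotgun metagenomics. The statistical methods in Supplementary Note 1 mention no mediator adjustment. This stands in part. It makes the harmless reading possible but does not establish it, because the section uses a separate term for covariates and gives no time points.

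A reader might also infer that any bias would usually run towards zero. That needs both same-sign paths and no confounding between mediator and taxon. The documents establish neither, and the null example above shows the opposite error.

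**Conclusion.** The point holds in a limited and conditional form. The plan states an adjustment step for potential mediators without naming or timing them, and does not say which taxa model answers the between-arm question. If any of those variables is measured after randomisation and affected by the supplement, the adjusted arm coefficients do not estimate the randomised effect and may be biased in either direction. If all are fixed at or before randomisation, that bias does not arise and only the wording needs correcting.

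The size cannot be derived from the documents. The illustrative figures rest wholly on the assumed effect, arm–mediator effect, correlation and loadings, and show only that the error could matter. The reach is small: a secondary outcome, with the crude estimate also planned and the primary chair-rise model unaffected by this sentence. This is a low-priority improvement.

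**What to change.** Replace the mediator sentence in the SAP, and align protocol 17.2, as follows.

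1. Estimate the arm effect on each taxon with end-of-study abundance as the outcome, adjusted for baseline abundance. The taxa plan does not currently state this covariate, although the SAP does for metabolites and the functional outcomes.
2. Limit other adjustment to variables fixed at or before randomisation (age, sex, baseline diet, baseline activity) plus technical covariates such as library size.
3. Name that model, or the crude model, as the basis for the between-arm conclusion on taxa.
4. Report any mediator-adjusted models separately as exploratory mediation analyses, listing each mediator and its time point.

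The cost is SAP wording. The main arm comparison needs fewer models and no new data, since stool samples are already planned at the start and end of the study. In the illustration, baseline adjustment left the estimate unchanged and raised power.

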### ***c. Sensitivity Analyses***

If necessary, sensitivity analyses will be conducted to assess the impact of poor adherence (self-reported), missing data, outliers and/or unexpected imbalances between the two groups at baseline. These analyses will be compared to the primary analyses to assess any differences in conclusions.

### ***d. Missing data***

#### ***i. Missing outcome data***

We will follow a four-point framework for dealing with incomplete observations which will allow the correct method to be chosen and subsequently implemented .

1. Attempt to follow up all randomised participants, even if they withdraw from allocated treatment
2. Perform a main analysis of all observed data that is valid under a plausible assumption about the missing data. Specifically, we will assume data is missing at random (MAR). Under this assumption, imbalances between treatment groups due to dropout can be corrected by appropriate multiple regression models.
3. Perform a sensitivity analysis to explore the effect of departures from the assumption made in the main analysis. The MNAR (missing not at random) analysis will use the method of White et al. (2011) .

#### 4. Account for all randomised participants, at least in the sensitivity analyses

This framework highlights the importance of using plausible assumptions with regards to the nature of the missing data. These assumptions will then be tested using appropriate sensitivity analyses on observed data using complete cases analysis. For the purpose of the main analysis, we will assume that missing data is missing at random, and the effect of the intervention is the same in those with and without the observations. Furthermore, we will check whether there is an imbalance or is similar the percentage of missing data within each treatment allocation.

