|--------------------------------------|------------------------------------------------------------------------------------------------------------------------------------------------------------------------------------------------------------------------------------------------------------------------------------------------------------------------------------------------------------------------------------------------------------------------------------------------------------------------------------------------------------------------------------------------------------------------------------------------------------------------------------------------------------------------------------------------------------------------------------------------------------------------------------------------------------------------------|
| Number of Subjects/Patients          | The sample size has been calculated to detect effect in chair-rise time; 70 individuals will have 80% power at 0.05 alpha to identify a difference of 3.5 seconds (effect size in 35 people per group, over 12 weeks) (20% dropout rate).                                                                                                                                                                                                                                                                                                                                                                                                                                                                                                                                                                                    |

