### ***Sample size calculation***

From our existing data, we have observed that chair-rise time is to a good approximation log normal, with  $\log_{10}(\text{time})$  having a SD of 0.126. We consider a relative reduction in average time of 20% to be both clinically important and plausible. Based on these figures, we would need complete data on 30 subjects per group (60 in total) for 80% power. Allowing for 20% dropouts, we would need 70 (35 per group) recruited. Based on the numbers we plan to recruit for the study, we estimate a recruitment time period of 18 months.

We have estimated a powered sample size based on other studies using chair-rise time, however we note that no study has looked at this in the context of protein and/or prebiotic food supplementation and therefore may not be accurate.

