## 5. Analysis Populations

Intention-to-treat (ITT) will include all randomised study subjects. This will be seen as the primary population for the analysis.

Per Protocol (PP) will include all randomised study subjects completing the whole study period (complete cases). For a specific analysis, study subjects with missing data on any of the variables in the model will be excluded from the analysis. Analyses of this population is seen as a sensitivity analysis to investigate whether conclusions are sensitive to assumptions regarding the pattern of missing data.

In our study, those who have not completed both study visits will be excluded from PP analysis. In addition, those who have lower than 50% adherence to the study intervention will also be excluded.

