### **i. Primary Outcome**

The primary analysis will compare intervention groups (arm 1 vs arm 2; blinded) on their change in chair rise time at 12 weeks using a linear mixed model. Chair rise time at 12 weeks will be the dependent variable. Twin clustering will be considered as random effects, treatment group as fixed effect. Baseline value of chair rise time will be included as a covariate [See: ]. If, despite randomisation, there is a difference between the two arms for a specific baseline characteristic, for example age, then age will be included as a covariate in the linear mixed models. The estimated difference in mean change from baseline to 12 weeks and the corresponding 95 % confidence interval (CI) will be presented.

The nature of the design of this study, with randomisation by twin pair and therefore clustering within the data will be taken into consideration by using both twin pair identifier (fid) and zygosity as random effects.

The number of participants who experience a 20% reduction in their chair rise time, as has been deemed clinically significant in previous studies (See Section 3.3), will be presented. We acknowledge that none of these studies used an intervention targeting the gut microbiota, however none such studies were available, making these the closest benchmark available.

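### The SAP presents the complete-case/per-protocol analysis as the test of its missing-at-random assumption, but people with no 12-week chair rise time are absent from that analysis and from the primary one

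*Combined protocol and SAP*

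**What the plan says.** Section numbers follow the SAP's contents page.

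- **Primary model (SAP 7.2.1, Primary Outcome).** "Chair rise time at 12 weeks will be the dependent variable". Baseline chair rise time is a covariate, treatment is a fixed effect, and twin pair and zygosity are random effects.
- **Analysis sets (SAP 5).** Intention to treat (ITT) is all randomised subjects. Per protocol (PP) is those who complete the study, labelled complete cases, minus anyone missing a model variable and anyone below 50% adherence. On its purpose: "Analyses of this population is seen as a sensitivity analysis to investigate whether conclusions are sensitive to assumptions regarding the pattern of missing data".
- **Missing outcomes (SAP 7.5.1).** A four-point framework: (1) try to follow up everyone, including those who stop treatment; (2) run the main analysis on the observed data under MAR; (3) run a sensitivity analysis for departures from MAR, using a cited MNAR method; (4) account for all randomised participants, at least in the sensitivity analyses. The closing paragraph then says of the assumptions: "These assumptions will then be tested using appropriate sensitivity analyses on observed data using complete cases analysis". It also plans to compare the percentage missing between arms.
- **Missing baseline covariates (SAP 7.5.2).** These are imputed, so people with an outcome stay in the analysis.
- **Sensitivity analyses (SAP 7.3).** "If necessary, sensitivity analyses will be conducted to assess the impact of poor adherence (self-reported), missing data", followed by outliers and baseline imbalance. No trigger is given.

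**The concern.** A check on a missing-data assumption is useful only if its result could change when the assumption fails. Here the main analysis and the complete-case analysis both leave out the people whose outcomes are unknown. If those people did better or worse than the model predicts, both estimates are wrong by about the same amount and still agree. Under the wording of SAP 5 and 7.5.1, that agreement could be reported as evidence that missing data do not matter.

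The analysis that can address the question is the MNAR analysis in item 3. Section 7.3 leaves room to skip it, and the SAP gives no departure values for it. The same model serves other outcomes, including cognition, where Supplementary Table S3 shows 46 of 72 participants without CANTAB results at study end. That figure says nothing about chair rise time, but it shows that the wording could matter for other outcomes.

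**Working it through.** **1. Who is in each analysis of chair rise time**

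| Participant | Primary model (7.2.1, 7.5.1 item 2, 7.5.2) | Complete-case/PP (SAP 5) |
|---|---|---|
| No 12-week value | No row | No row |
| 12-week value, a baseline covariate missing | In, covariate imputed | Out |
| 12-week value, below 50% adherence or study period not completed | In | Out |
| 12-week value, complete and adherent | In | In |

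The sets differ only in rows two and three, and everyone in those rows has an observed outcome. The first row, the only one to which the missing-outcome assumption applies, is the same in both. A co-twin who has a 12-week value is judged separately and does not bring the absent twin back. If rows two and three are empty, the two analyses use identical data and must give the same estimate, whatever the reason for the missing values.

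**2. The plan's own figures, used only to scale an illustration**

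- Significance level and power: "70 individuals will have 80% power at 0.05 alpha to identify a difference of 3.5 seconds" (protocol synopsis). Sidedness is not stated, so two-sided is assumed.
- SD: log10(time) "having a SD of 0.126" (SAP 3.3).
- Effect: "We consider a relative reduction in average time of 20% to be both clinically important and plausible". On the log10 scale, −log10(0.8) = 0.0969. Standardised, 0.0969 / 0.126 = 0.769.
- Stated size: "we would need complete data on 30 subjects per group (60 in total) for 80% power", then 70 recruited to allow for 20% dropout.

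Per group, n = 2 × (1.960 + 0.842)² × 0.126² / 0.0969² = 26.5, so 27 by the normal formula; the two-sample t-test gives 28. The stated 30 is slightly conservative. With 28 per group, 56 / 0.8 = 70 exactly; with 30, 60 / 0.8 = 75. The planned missing fraction is therefore either the stated 20% or the (70 − 60) / 70 = 14.3% implied by 60 complete out of 70. Both are carried forward. Nothing in step 1 depends on them.

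**3. What an MNAR analysis could show and the complete-case analysis cannot**

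Let f be the fraction missing in an arm, and δ the amount by which the mean of the missing outcomes departs from the MAR prediction. The estimated difference then moves by approximately f₁δ₁ − f₂δ₂. The documents give no δ. Taking it as an assumption from 0 to the design effect, in one arm only:

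- f = 14.3%: 0.143 × 0.0969 = 0.0138 log10 at most, or 14% of the design effect (10^0.0138 = 1.032, about 3% in time).
- f = 20%: 0.20 × 0.0969 = 0.0194 log10 at most, or 20% of the design effect (10^0.0194 = 1.046, about 5% in time).

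Opposite departures in the two arms would double these, to 29% and 40%. The movement that a complete-case analysis can show for people with missing outcomes is 0 in every case.

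**4. The planned comparison of percentages missing**

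With f₁ = f₂ = 20% and a departure in one arm only, the percentages match while the estimate is off by up to 0.0194. Equal percentages do not establish MAR.

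**The case against.** **The SAP already plans the right analysis.** This is the strongest reply, and it stands. Item 3, shortly before the sentence at issue, commits to an MNAR analysis by a cited method, and item 4 requires all randomised participants to be accounted for. A reader might infer that the complete-case comparison is the SAP's only check on missing data; the documents do not support that. What remains is that two sections credit the complete-case/PP analysis with a property it lacks.

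**ITT is not abandoned.** A reader might also infer that the promised ITT analysis is silently replaced by completers. Items 2 and 4 state openly that the main analysis uses observed data and that full accounting comes in the sensitivity analyses.

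**ITT and PP can differ because of withdrawals.** This is true of people who stop treatment but return for the final visit, as item 1 intends: they are in ITT and may be outside PP. It would be too strong to say that the comparison never reflects withdrawals. It never reflects those without a 12-week value.

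**The conditional wording is generic.** Section 7.3 covers several issues in one sentence, while 7.5.1 is unconditional and the planned outputs include a sensitivity table. The likely intent is to run the work if data are missing. Even so, the two sections conflict as written, and the table entry does not say which analyses fill it.

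**The size is assumed.** This is accepted. Step 3 is an identity with a chosen δ, not evidence of bias. The largest one-arm shift, 0.0194, is about 0.6 of an unadjusted standard error (0.126 × √(2/28) = 0.034), and no changed conclusion is shown. Whether the cited method prescribes departure values cannot be judged from these documents.

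**Protocol Stage 6 mentions repeated measures mixed modelling.** If baseline were an outcome record, a dropout's baseline would contribute. The SAP specifies the 12-week model instead. Even under repeated measures, a comparison with complete cases would not test departures from MAR, because the unseen values still would not enter.

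**Conclusion.** The point holds in a limited form. For chair rise time, the complete-case/PP analysis cannot test the MAR assumption, because people without a 12-week value are in neither analysis. That follows from SAP 5, 7.2.1, 7.5.1 and 7.5.2 read together and needs no numerical assumption. Separately, 7.3 makes conditional what 7.5.1 states without condition.

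The documents do not show that the primary result is biased. They do not report how many participants lacked a 12-week chair rise time. The illustrative shift, 0 to between 0.014 and 0.019 log10 (up to 14% to 20% of the design effect), rests on three assumptions: the planned missing fractions, a departure in one arm of no more than the design effect, and analysis on the log10 scale used for the sample size. This is a correction that should be made; it does not invalidate the design.

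**What to change.** - **SAP 5 and 7.5.1:** delete the statements that the complete-case/PP analysis tests the missing-data assumption. Describe PP as an adherence and completer analysis.
- **SAP 7.5.1:** name the MNAR analysis already planned in item 3, covering all randomised participants as in item 4, as the check on MAR for chair rise time.
- **SAP 7.3:** remove the conditional wording for missing data, so that the MNAR analysis is run whenever any 12-week chair rise time is missing.
- **Departure values:** fix them before unblinding, including values applied to one arm at a time, and report the value at which the conclusion changes. The range is for the trial team to justify; 0 to 0.097 log10 above is only an example. If unblinding has already happened without values being set, report the analysis and label the values post hoc.
- **Reporting:** give the number without a 12-week chair rise time in each arm.

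The cost is SAP wording and one analysis run with a method that the SAP already cites. No new data are needed.
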